#### Cost accounting analyses

Costs have to be integrated with obtained quality and quantity of life in order to measure the significance of an intervention on a person and society. Cost-utility analyses, which are a type of cost-effectiveness analyses estimate cost per QALY (Quality-adjusted life year) gained and are based on health-related quality of life measures [52,53]. Treatment costs will be evaluated for each type of management. Cost utility analysis at one and two-year follow-ups are based on SF 6D (derived from SF 36) and costs measured with cost-diary. The mean for health-related quality of life measure at baseline, 12 and 24 months are determined [50]. The mean gain is then calculated. Also cost-per-quality-adjusted-life-year (QALY) will be evaluated for clinical benefits for total lifetime costs from each group.

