### Data management

Intention-to-treat analysis [51] with per protocol method is used in all the calculations. Per protocol method is chosen because of the nature of the acute condition, i.e. all patients are expected to get better. Descriptive statistics and appropriate multivariate analyses (Linear Mixed Models) will be used to decrease type I error in analyses of group differences over time. The Linear Mixed Models permit correlations (due to repeated measuring over time) between variables and can handle the missing values in a proper way.

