### Study size and Power calculations for the sample

The power calculation is based on repeated three-group analysis. Since there are no previous studies to compare with, the power calculation is based on hypothetical reasoning of effects. Upon completion of treatment, all groups will be assumed to have achieved 75 per cent improvement in the main outcome variable, Pain Disability Index, compared with the baseline levels. We assume that at the one-year follow-up, standard-treatment group will have lost 75 percent of improvement and group 1 and 2 25 percent of improvement. This gives a long-term effect size which is >.80. At a significance level of .05, a two-tailed analysis requires 60 people in each group to attain a statistical power of .90. Time needed to include approximately 200 patients (including possible drop-outs) with these inclusion criteria is expected to take at least 1,5 to 2 years according to empirical experience.

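### The cost-utility gain, built from SF-6D means at baseline, 12 and 24 months, is unprotected against withdrawal that is related to utility and differs between arms

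*Protocol article*

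**What the plan says.** The Cost accounting analyses section names its sources: "Cost utility analysis at one and two-year follow-ups are based on SF 6D (derived from SF 36) and costs measured with cost-diary". It then gives the calculation: "The mean for health-related quality of life measure at baseline, 12 and 24 months are determined [50", followed by "The mean gain is then calculated". It does not say whether the gain is formed within each patient or as a difference between visit means, nor who is in each mean. It mentions no model and no adjustment for baseline utility.

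The Data management section sets the analysis population: "Intention-to-treat analysis [51] with per protocol method is used in all the calculations". On the model it says that "appropriate multivariate analyses (Linear Mixed Models) will be used to decrease type I error in analyses of group differences over time", and that these models "can handle the missing values in a proper way".

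The Cost accounting measures section draws direct medical costs from medical records and from self-report, and indirect costs from self-report. The diary covers four weeks.

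On losses, the sample-size section asks for 60 patients per group and says: "Time needed to include approximately 200 patients (including possible drop-outs) with these inclusion criteria is expected" to take at least 1.5 to 2 years. It gives no rate by arm or by visit.

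**The concern.** Finding the most cost-effective of the three interventions is a stated goal of the trial (Abstract and Hypothesis). The utility part of that result is described as raw means and a gain. Nothing in the description protects such a gain when the patients contributing at 12 and 24 months are a selected part of those measured at baseline.

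Withdrawal could plausibly differ between arms. By the Intervention section, Internet patients must finish one module before opening the next, face-to-face patients meet a therapist seven times, and standard-care patients receive nothing further. If patients in poorer health also leave more readily, the arms would be compared on differently selected survivors. The resulting QALY difference is the denominator of the cost per QALY, so a small false difference can matter to the ranking of the three arms.

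**Working it through.** The plan states no SF-6D mean, SD, QALY or withdrawal rate, so there is no figure of its own to reproduce. What can be checked is the mechanism and its size under stated assumptions.

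**Input from the document.** Required: 3 × 60 = 180. Recruited: about 200. Implied loss: 1 − 180/200 = 10% overall.

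**Bias within one arm.** Let d be the share who leave, B and F the baseline and follow-up means, and S and L stayers and leavers. The target is the gain in all randomised patients, F_all − B_all, with F_all = (1 − d)F_S + d·F_L.

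- Gain in visit means over available patients: F_S − B_all. Bias = F_S − F_all = d × (F_S − F_L), the dropout share times the *follow-up* difference between stayers and leavers.
- Gain paired in completers: F_S − B_S. Bias = d × (stayers' gain − leavers' gain).

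**Bias between arms.** For visit means it is d1·Δ1 − d2·Δ2, where Δ = F_S − F_L. With a common Δ it is (d1 − d2)·Δ. It vanishes if Δ = 0 or if the loss is the same in both arms.

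**Numbers, with Δ assumed to be 0.05 to 0.10.**

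- 5% against 15%: 0.10 × 0.05 = 0.005, to 0.10 × 0.10 = 0.010 utility.
- 10% against 30%: 0.20 × 0.05 = 0.01, to 0.20 × 0.10 = 0.02 utility.

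The first pair averages the implied 10%. The second exceeds it: even with no loss in the third arm, the overall rate would be (10 + 30 + 0)/3 = 13.3%.

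**Hand example.** Sixty patients, 30 constant at 0.55 and 30 constant at 0.75, so nobody changes. Twelve of the lower group leave before month 12.

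- The mean moves from 0.650 to (18 × 0.55 + 30 × 0.75)/48 = 0.675, a false gain of 0.025. The formula agrees: 12/60 × (0.675 − 0.55) = 0.025.
- As area under the means over two years: (0.650 + 0.675)/2 + 0.675 − 2 × 0.650 = 0.0375 QALY.
- The paired gain is correctly zero here, because the baseline difference persists unchanged.

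**Simulation when the difference does not persist fully.** There were 1,000,000 patients per arm and the same true course in both arms, so the true difference is 0. Assumed: SF-6D means 0.65, 0.72 and 0.74, SD 0.12, correlation between visits 0.5 or 0.7. Where selective, withdrawal was more likely with low baseline utility (log-odds 0.5 or 1.0 per SD). The outcome is the two-year area minus twice the baseline mean.

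| Withdrawal by 24 months | Visit means | Paired completers |
|---|---|---|
| Unrelated to utility, equal or unequal rates | about 0.000 | about 0.000 |
| Related to utility, same in both arms (18–19%) | about 0.000 | about 0.000 |
| Related to utility, 27–37% against 9–14% | +0.007 to +0.021 | −0.005 to −0.017 |

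Entries are the false QALY difference, arm with more loss minus arm with less. Visit means flatter the arm that loses more patients; pairing in completers penalises it. Pairing alone is therefore no cure.

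**The case against.** The strongest reply is that the defect is inferred. The article does not say that the baseline mean covers everyone and the later means only those still answering. Its sentence also fits a fixed analysis set, within-patient gains or model-based means. The population statement is worded to cover all calculations. SF-36 is a listed secondary outcome, so the mixed models might extend to the SF-6D derived from it. A journal article may also leave missing-data detail to a fuller document, and the sentence cites a source for the method.

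Much of this stands. Who is averaged is not stated, and silence on missing data would be no finding. A reader might infer that the clinical and economic results follow different missing-data rules and rest on different patients. The text does not support that: the economic section states no missing-data rule at all. A reader might also infer that any loss to follow-up distorts the QALY difference, or that this result is biased. Neither follows, since both conditions are needed and the document shows neither.

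What does not stand is that the remaining text resolves the matter. A calculation is written down, and it is means and a gain. The models are linked to group differences over time and are not mentioned in the economic section. The population label joins two approaches that normally select different patients. Both natural readings, available-patient means and paired completers, fail under the same conditions.

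**Conclusion.** The point holds as a weakness in a stated estimator for a main goal; it does not show that bias will occur. The incremental QALY is exposed if withdrawal is both related to utility and different between arms, and is unaffected if either condition fails.

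The size cannot be computed from the document. At loss rates consistent with the implied 10% overall, the shift is 0.005 to 0.010 utility; at 10% against 30%, it is 0.01 to 0.02. Both rest on an assumed follow-up difference of 0.05 to 0.10 between stayers and leavers, common to the arms. The simulated 0.007 to 0.021 QALY rests on assumed SF-6D values and on loss rates above the plan's allowance: with no loss in the third arm, 27% and 9% would still average 12%. The change should be made because it is cheap and improves on either reading of the current text.

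**What to change.** In Cost accounting analyses, replace the gain in raw means by an analysis of all randomised patients, in one of two ways:

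- a linear mixed model for SF-6D with baseline SF-6D included, preferably as one of the repeated measures so that patients without follow-up still contribute; or
- joint multiple imputation of SF-6D and costs by arm, then per-patient QALYs and costs, with QALYs adjusted for baseline SF-6D.

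Use the same patients for costs and QALYs. Where the cost diary is missing, use the medical-record costs already described in Cost accounting measures. Those records serve direct medical costs only, so self-reported items such as sick days still need imputation. State which patients enter in place of the combined intention-to-treat and per-protocol label.

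Both methods assume that withdrawal depends on observed data, so they reduce the problem and do not remove it if patients leave because of unrecorded deterioration. The cost is revised wording and some extra analysis work. No new data or patients are needed, and the first option uses a type of model the plan already employs.

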### Study Design

The study is a randomized, prospective, experimental three-group study with analyses of cost-effectiveness up to two-years follow-up (see Figure 1). IT- based programme (Group 1) and face-to-face group treatment programme (Group 2) are compared to standard-treatment only (Group 3) Patient follow-ups take place three, six, twelve and 24 months, that is, short-term as well as long-term effects are evaluated. Figure 1 presents the study design and patients' flow till now.

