### Study setting and Participants

Patients will be enrolled via the emergency ward during the first week after the accident. All patients get a letter from the emergency staff during they visit that explains the reason why they will be contacted by a physiotherapist. The emergency staff will also give standard treatment instructions for all patients. The second author will approach the patients by phone after receiving a list of patients that seek the emergency ward. During the phone call an informed consent is received. All eligible patients are scheduled to an appointment with the calling physiotherapist. During the appointment the patients that fulfil inclusion criteria will complete the baseline measures. Inclusion criteria for this study are age between 18 and 65, and satisfactory Swedish language skills. Patients are to fulfil criteria for the diagnosis of WAD grade I and II [1] and have ongoing pain in the neck due to the accident. Participants should also have access to a computer to be eligible for the study. Patients with prior neck injury, other ongoing chronic pain problems or ongoing treatment for pain or pain related symptoms are not eligible.

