The new IT-based treatment (Internet/e-mail) regimen for acute WAD patients, emphases self-monitoring and skills training, as well as discussions led by a therapist. The patient will be instructed when to start and how to log onto the Internet treatment modules (seven modules; A – G), one at a time and get individualized support via e-mail from a therapist. The patient cannot log onto the next module if she/he has not completed the tasks in the previous module. Questions from the patients as well as answers from the therapist will be available on the treatment site, by consent from the patient, functioning as an additional support for the fellow patients, i.e. virtual group treatment.

#### Group 2

Face-to-face intervention involves groups of three to six patients led by therapists. The therapist meets with the group seven times during the acute phase following the accident. The face-to-face programme is planned to be similar to the IT-based treatment regimen described above, but differs in the way the treatment is administered. The programme consists of those seven treatment phases in seven modules described above (Additional file 1).

#### Group 3

Standard care of these patients currently involves a visit to a physical therapist, which provides a home exercise programme dealing with physical symptoms and advice of returning to normal activities as soon as possible. No further treatment is given except the home exercise programme that all patients get at the emergency ward (standard care) before randomisation.

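### The QALY rule uses SF-6D at baseline, 12 and 24 months only, so the one-year QALY difference is misestimated, in a direction not fixed in advance, unless the arms diverge linearly over the first year

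*Protocol article*

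**What the plan says.** All references are to the protocol article.

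- **Cost accounting analyses** sets cost-utility analyses at one and two years, using SF-6D derived from SF-36. The utility rule is: "The mean for health-related quality of life measure at baseline, 12 and 24 months are determined", followed by "The mean gain is then calculated".
- **Study Design** has more visits than that: "Patient follow-ups take place three, six, twelve and 24 months". The Figure 1 caption also lists a measurement immediately after treatment, separate from the 3 to 24-month follow-up.
- **Secondary outcome** names SF-36 as the source for QALYs and ties it to no particular visit.
- **Study setting and Participants** places baseline in the acute phase: "Patients will be enrolled via the emergency ward during the first week after the accident". Treatment also falls early. For the face-to-face arm, **Intervention** says: "The therapist meets with the group seven times during the acute phase following the accident".
- **Study size and Power calculations for the sample** sets out the expected course: "Upon completion of treatment, all groups will be assumed to have achieved 75 per cent improvement in the main outcome variable". By one year, standard care is assumed to lose 75% of that improvement and the two behavioural arms 25%.

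**The concern.** A QALY total is utility accumulated over time. With values at 0, 12 and 24 months only, the first year becomes a straight line from the week of the accident to month 12. The trial's own planning assumption is not a straight line: the arms are level at end of treatment and separate afterwards. The turning point lies inside the interval that the rule skips.

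Finding the most cost-effective of three interventions is a stated goal, and the QALY difference is the denominator of cost per QALY. With the cost difference held fixed, a denominator 33% too high makes the ratio 25% too low (1/1.333 = 0.75). A denominator 20% too low makes it 25% too high (1/0.80 = 1.25). The article also promises to evaluate short-term effects, but this rule cannot register a short-term utility benefit that has faded by 12 months.

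**Working it through.** The article states no QALY figure, so there is none to reproduce. The check applies the stated time points to the article's own expected course.

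**Inputs from the article.** Improvement at end of treatment is 0.75 in every arm. At 12 months standard care keeps 0.75 × 0.25 = 0.1875 and the behavioural arms keep 0.75 × 0.75 = 0.5625.

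**Assumptions, not in the article.** Utility gain is proportional to improvement in the Pain Disability Index, and U is the utility gain for 100% improvement. Visit times count from baseline. Treatment ends at 3 months (varied below). The course is flat from 12 to 24 months.

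**Step 1: what cancels.** Year-1 area with treatment end at 3 months and linear relapse:
- Standard care: 0.5 × 0.75 × 0.25 + 0.5 × (0.75 + 0.1875) × 0.75 = 0.4453U. From baseline and 12 months only: 0.5 × 0.1875 = 0.0938U. Missed: 0.3516U.
- Behavioural arm: 0.5 × 0.75 × 0.25 + 0.5 × (0.75 + 0.5625) × 0.75 = 0.5859U. From baseline and 12 months only: 0.5 × 0.5625 = 0.2813U. Missed: 0.3047U.

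Most of the missed area is common to both arms. The error in the difference is 0.3516 − 0.3047 = 0.0469U.

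**Step 2: the difference between arms.** It is 0 at baseline, 0 at end of treatment and 0.5625 − 0.1875 = 0.375U at 12 months. The stated time points always give 0.5 × 0.375 × 1 = 0.1875U in year 1 and 0.1875 + 0.375 = 0.5625U over two years. The area under the assumed course depends on when relapse occurs:

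| Relapse | Year-1 area | Year-1 error | Two-year area | Two-year error |
|---|---|---|---|---|
| Linear, 3 to 12 months | 0.5 × 0.375 × 0.75 = 0.1406U | +33% | 0.5156U | +9% |
| Complete by 6 months | 0.5 × 0.375 × 0.25 + 0.375 × 0.5 = 0.2344U | −20% | 0.6094U | −8% |
| Starts only after 6 months | 0.5 × 0.375 × 0.5 = 0.0938U | +100% | 0.4688U | +20% |

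**Step 3: end of treatment.** With linear relapse the year-1 ratio is 1/(1 − T), with T the end of treatment in years. At 7 weeks (T = 7/52 = 0.135, which assumes weekly meetings) the error is +16% in year 1. Over two years it is 0.5625/(0.1875 × 0.865 + 0.375) = 1.05, or +5%. At 2 months the three patterns give +20%, −25% and +100% in year 1.

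**Step 4: absolute size.** U is not in the article. For an assumed U of 0.1 to 0.3, the linear-relapse error in year 1 is 0.0469 × U = 0.005 to 0.014 QALY per patient.

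**Step 5: two boundary cases.** If the difference grows linearly from baseline to 12 months, the error is zero. If instead one arm has a utility advantage d at 3 and 6 months that is gone by 12, the true area is d × (0.5 × 0.25 + 0.25 + 0.5 × 0.5) = 0.625d. For an illustrative d of 0.05 to 0.10 that is 0.031 to 0.063 QALY, and the stated time points give zero.

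**The case against.** The strongest reply is that the effect is modest and unsigned. Several parts of it stand.

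- **Shared recovery cancels.** A reader might infer that skipping the acute recovery phase biases the result in itself. It does not: the sample-size section assumes equal improvement in all arms at end of treatment, and only the later divergence matters.
- **No fixed direction.** A reader might infer that the rule flatters the behavioural arms. The article does not say when relapse occurs, and early relapse reverses the sign.
- **The 33% rests on an assumed 3-month end of treatment.** The Figure 1 caption lists post-treatment and 3-month measurements separately, so treatment may end sooner and the linear-relapse error would be smaller.
- **The early-only benefit is an illustration.** It departs from the article's assumption of equal improvement at end of treatment.
- **The mean gain might be read as a raw change score used as a QALY.** That would give 0.375U against 0.1406U, or 2.7 times too high. The text does not settle this. The section speaks of cost per QALY gained and cites a source that is not available here, and a condensed article may leave the conversion to an area to a fuller document.
- **Whether SF-36 is completed at 3 and 6 months is not stated,** so it cannot be said that collected data are being discarded.

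What does not stand is that the whole matter is a detail left to another document. The article itself names the utility time points, and these leave out two scheduled follow-ups.

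**Conclusion.** The point holds as a limited one that should be changed. The stated time points give the right one-year QALY difference only if the arms diverge linearly from baseline to 12 months (or if early and late departures from that line happen to balance), whereas the article plans on a different course. The size, for a behavioural arm against standard care, is that tabulated in the working: appreciable for the one-year analysis and much smaller for the two-year analysis. It depends on proportional utility, the assumed end of treatment, the timing of relapse and a flat second year. The article assumes the same course for the Internet and face-to-face arms, so these figures put no size on that contrast; the rule would misestimate it only if the two arms departed from each other non-linearly. The documents support neither a claim of systematic overstatement nor one of a 2.7-fold error.

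**What to change.** Replace the sentence that names the utility time points, and the one on the mean gain, with a rule such as: each patient's QALYs are the area under the SF-6D curve by the trapezoidal rule over all visits at which SF-36 is completed (baseline, post-treatment if measured, 3, 6, 12 and 24 months), and arms are compared with adjustment for baseline SF-6D.

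The post-treatment value is worth using where it exists. If treatment ends at 2 months, the grid of baseline, 3, 6, 12 and 24 months is itself about 2% too high with linear relapse (0.1594U against 0.1562U) and 3% too high with relapse complete by 6 months (0.2578U against 0.2500U).

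If SF-36 is already completed at 3 and 6 months, the cost is wording and a little analysis. If not, add it to those existing follow-ups: one extra questionnaire at two visits. Figure 1 shows patient flow to date, so some patients may already be past those visits. Their values would be missing and would have to be handled as such.

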### Study size and Power calculations for the sample

The power calculation is based on repeated three-group analysis. Since there are no previous studies to compare with, the power calculation is based on hypothetical reasoning of effects. Upon completion of treatment, all groups will be assumed to have achieved 75 per cent improvement in the main outcome variable, Pain Disability Index, compared with the baseline levels. We assume that at the one-year follow-up, standard-treatment group will have lost 75 percent of improvement and group 1 and 2 25 percent of improvement. This gives a long-term effect size which is >.80. At a significance level of .05, a two-tailed analysis requires 60 people in each group to attain a statistical power of .90. Time needed to include approximately 200 patients (including possible drop-outs) with these inclusion criteria is expected to take at least 1,5 to 2 years according to empirical experience.

